#### Sexual health action plan

The action plan is based on the outcome of the annual systems assessment and is developed by health services supported by STRIVE coordinators to guide strategies for the health services over the next year of the trial and aimed at improving sexual health service delivery. The strategies may involve better application of existing procedures. For example discussion of STI best practice at weekly service meetings and regular data review, or new innovations such as STI testing visual reminder cards placed in clinics; implementing systematic approaches for collection of urine specimens and ensuring electronic recalls are installed within patient information management systems. The action plan is reviewed at three months and updated six monthly following the site visits.

#### Indicator reports

Health service staff and managers are provided with six monthly reports based on the best practice indicators, to discuss at the feedback meetings. These quantitative reports show the extent of improvements towards the targets. In addition to the best practice indicators, the reports also provide information on the proportion of community residents in the target age group who attended the health service during the period. Population denominators are derived from the number of Aboriginal residents who attended the health service in the preceding two years.

#### Clinical performance payments

After randomisation to the SHQIP, health services receive incentive payments on a six monthly basis, except for testing coverage, which is assessed annually. Payments are calculated on the basis of progress towards best practice targets. Services receive payments of $100 (AUD) for each episode of treating patients with STI symptoms at consultation; for treating a person diagnosed with an STI within seven days of the laboratory result being received at the clinic; and for re-testing each individual diagnosed with an STI at three months. Services also receive $100 per contact tested and treated within two weeks of being named. For a 10% or more improvement in any indicator in the subsequent period, the service receives a $500 payment. Services which reach the targets receive an additional $500, once only.

### Data collection methods and variables

The trial uses a number of methods to collect data (Table 2).

**Table 2 T2:** Tools, methods and description of information collected in the trial

**Tool**	**Method and frequency**	**Description of data collected**
Site description assessment	• Conducted by regional STRIVE Coordinators at baseline and the start of each year in all health services	*Broad description of:*
	• Updated annually with any contextual information that may impact on delivery of STI services	(i) Current sexual health activities, including health promotion activities
Systems Assessment	• Conducted by regional STRIVE Coordinators annually in health services randomised to the SHQIP	*Information on:*
		(i) Health hardware
		(ii) Clinical services
		(iii) Patient information systems
		(iv) Health promotion
		(v) Organizational commitment to sexual health
		(vi) Surveillance and evaluation
Quantitative STI testing and clinical management data	• Collated from one or more of the following sources:	(i) Patient consultation data and associated demographics
	(i) Health service patient information management systems	(ii) STI testing, retesting and treatment outcomes Laboratory test result
	(ii ) STI templates within patient management systems	
	(iii) Contact tracing forms	
	(iv) Laboratory data	
	• Extracted 6 monthly for all health services	
STI prevalence assessment	• Each person attending the clinic aged 16-34 will be offered a STI screening test for all three STIs	(i) Prevalence of chlamydia, gonorrhoea and trichomonas in 16-34 year olds in STRIVE trial clusters
	• 50 men and 50 women from each cluster will be included	
	• Takes place on an annual basis in all health services	

### Prevalence assessment

At the start of each year and prior to initial randomisation the prevalence of chlamydia gonorrhoea and trichomonas will be assessed in clients attending participating health services. The assessment will involve screening 50 male and 50 female resident clients aged 16–34 years per cluster. All those in the age group attending the health service in the prevalence assessment period will be offered testing, unless they have had a test within the preceding three months. For clusters with more than one primary health care centre, the target numbers of 50 men and women will be allocated proportionately according to the number of health services and the size of the community served. The prevalence will be assessed again at the end of the study (Figure 1).

### Outcome measures

Primary outcomes are:

1. Prevalence of chlamydia, gonorrhoea or trichomonas in male and female Aboriginal residents aged 16–34 years, as measured using the trial prevalence assessment (Table 2); and

2. Performance in clinical service activity based on the best practice indicators over the period of the trial (Table 1).

All outcomes will be calculated by cluster, service, gender, patient age group (16–19, 20–24, 25–29, 30–34 years), STI type, and the reason for attendance.

Secondary outcomes are:

1. Diagnoses of pelvic inflammatory disease (PID) and epididymitis

2. Feasibility and acceptability of research conducted in remote primary care settings.

### Sample size

Power calculations were performed using the method of Hayes and Bennet [34] for cluster randomised trials. Estimates of between and within cluster variability in the primary end point were based on prevalence of the selected STIs in 2006 (the most recent prevalence data available) among Aboriginal people aged 14–34 years in central Australia [35]. Prevalence of chlamydia and gonorrhoea was estimated to be 15%, with an average 65 people tested in each cluster for chlamydia and gonorrhoea. Based on the 2006 notification data, between community variability was estimated as corresponding to a standard deviation of 8.45%, and the within community co-efficient of variation of 0.42. A total of 14 clusters are needed to detect a reduction in chlamydia and gonorrhea prevalence from 15% in control clusters to 7.5% in SHQIP clusters with 80% power and allowing for differing average numbers of people screened in each cluster (2-alpha = 0.05, with no adjustments for multiple comparisons), and equal numbers of clusters in each arm.

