**Methods/design:**

STRIVE is a stepped-wedge cluster randomised trial designed to compare a sexual health quality improvement program (SHQIP) to usual STI clinical care delivered in remote primary health care services. The SHQIP is a multifaceted intervention comprising annual assessments of sexual health service delivery, implementation of a sexual health action plan, six-monthly clinical service activity data reports, regular feedback meetings with a regional coordinator, training and financial incentive payments. The trial clusters comprise either a single community or several communities grouped together based on geographic proximity and cultural ties. The primary outcomes are: prevalence of chlamydia, gonorrhoea and trichomonas in Aboriginal residents aged 16–34 years, and performance in clinical management of STIs based on best practice indicators. STRIVE will be conducted over five years comprising one and a half years of trial initiation and community consultation, three years of trial conditions, and a half year of data analysis. The trial was initiated in 68 remote Aboriginal health services in the Northern Territory, Queensland and Western Australia.

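### The stated 80% power is for chlamydia and gonorrhoea, but the primary prevalence outcome also counts trichomonas, so no power is given for the endpoint as defined

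*Protocol article*

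**What the plan says.** Outcome measures, in the protocol article, defines the first primary outcome as "Prevalence of chlamydia, gonorrhoea or trichomonas in male and female Aboriginal residents aged 16–34 years, as measured using the trial prevalence assessment". The abstract lists the same three infections joined by a different word: "prevalence of chlamydia, gonorrhoea and trichomonas in Aboriginal residents aged 16–34 years". Outcome measures adds a breakdown that includes infection type: "All outcomes will be calculated by cluster, service, gender, patient age group", and so on.

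Sample size describes its variability estimates as those of the primary endpoint, but every prevalence and effect figure in it is for two infections. The control value is "Prevalence of chlamydia and gonorrhoea was estimated to be 15%, with an average 65 people tested in each cluster for chlamydia and gonorrhoea". The target is to "detect a reduction in chlamydia and gonorrhea prevalence from 15% in control clusters to 7.5% in SHQIP clusters with 80% power". Trichomonas is not named in that section.

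The limitations paragraphs that close the Statistical analysis plan section then say that the study is powered for a 50% decline in STI prevalence, without saying which infections are meant.

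**The concern.** A power statement belongs to one endpoint, with its own control prevalence, between-cluster variation and expected effect. Here those inputs describe one endpoint and the primary outcome is another. Someone who is trichomonas-positive only counts as a case in the primary outcome and was not in the planning figures. Such people raise the control prevalence, and how they respond to the quality improvement program (SHQIP) determines whether the relative reduction stays at 50% or shrinks.

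Interpretation is at stake. If the composite result is null, a reader who trusts the stated power may conclude that a halving of chlamydia and gonorrhoea has been ruled out. In fact the composite could have been diluted by a component that the calculation never considered.

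**Working it through.** **Inputs from the protocol article.** Control prevalence p0 = 0.15 and intervention prevalence p1 = 0.075 (chlamydia and gonorrhoea); m = 65 tested per cluster; coefficient of variation k = 0.42; two-sided alpha 0.05; 80% power; 14 clusters in total (all Sample size). Study design has 24 clusters randomised in thirds. The two main analyses compare first with second round and first with third round clusters, so each is 8 v 8. Planned screening is 100 per cluster: "The assessment will involve screening 50 male and 50 female resident clients aged 16–34 years per cluster".

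**Inputs assumed.** The documents give no prevalence, between-cluster variation or expected response for trichomonas. I let trichomonas-only positives add 3, 5 or 10 points in control clusters and fall by 0, 25, 40 or 50% under the program. Chlamydia/gonorrhoea halves throughout, and k = 0.42 is kept for the composite.

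**Step 1: the plan's own figure.** With V = p0(1−p0)/m + p1(1−p1)/m + k²(p0² + p1²), the Hayes–Bennett number per arm is

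c = 1 + (1.96 + 0.84)² × V / (p0 − p1)².

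V = 0.001962 + 0.001067 + 0.004961 = 0.007990, so c = 1 + 7.849 × 0.007990 / 0.005625 = 12.15. That is 13 per arm or 26 in total, not 14 in total. The stated figure does not reproduce even for the two infections. That is a separate problem, so the comparisons below start from recomputed power, not from 80%.

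**Step 2: power at 8 v 8.** Noncentrality d = (p0 − p1)/√(V/8), two-sided t test on 14 degrees of freedom.

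Two infections, 15% to 7.5%, m = 65: d = 0.075/√(0.007990/8) = 2.37, power 60%. At m = 100 it is 66%.

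**Step 3: the three-infection composite.** Control prevalence is 15% + a and intervention prevalence is 7.5% + a(1 − r), where a is the trichomonas-only addition and r its relative fall.

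| a (points) | r | Composite | Relative reduction | Power, m = 65 | Power, m = 100 |
|---|---|---|---|---|---|
| 3 | 0% | 18% to 10.5% | 42% | 46% | 50% |
| 3 | 25% | 18% to 9.75% | 46% | 54% | 59.5% |
| 3 | 40% | 18% to 9.3% | 48% | 60% | 65% |
| 3 | 50% | 18% to 9% | 50% | 63% | 68% |
| 5 | 0% | 20% to 12.5% | 37.5% | 39% | 42% |
| 5 | 25% | 20% to 11.25% | 44% | 52% | 56% |
| 5 | 40% | 20% to 10.5% | 47.5% | 60% | 64% |
| 5 | 50% | 20% to 10% | 50% | 65% | 70% |
| 10 | 0% | 25% to 17.5% | 30% | 27% | 29% |
| 10 | 25% | 25% to 15% | 40% | 46% | 50% |
| 10 | 40% | 25% to 13.5% | 46% | 60% | 63% |
| 10 | 50% | 25% to 12.5% | 50% | 68% | 72% |

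Example, 25% to 17.5% at m = 65: V = 0.002885 + 0.002221 + 0.016427 = 0.021533, d = 0.075/√(0.021533/8) = 1.45, power 27%.

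The break-even fall in trichomonas is about 40% at m = 65 and about 43% at m = 100.

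**The case against.** The strongest reply is that the documents give no reason to expect trichomonas to respond less than the other two. Table 1 sets the same testing, treatment, re-testing and contact targets for all three, and Study design describes all three as easy to diagnose and treat. With an equal halving and the same k, adding trichomonas raises power a little. This stands: a reader might infer that the mismatch makes the trial weaker, but the documents do not support that. The 27% figure is the end of the range at which trichomonas does not respond at all. One detail points the other way: Best practice STI indicators describes the re-infection test for gonorrhoea and chlamydia only, although Table 1 includes trichomonas.

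A reader might also charge the whole drop from 80% to the lower figures to trichomonas. That would be wrong. The step from 80% to 60% is there before trichomonas enters and comes from the cluster count in Step 1.

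Two other differences may look like faults and are not. Planning on 65 when 100 are to be screened is conservative. Source data "among Aboriginal people aged 14–34 years in central Australia" are described as the most recent available, and using a nearby age band is ordinary planning.

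On one test or three, the definition with "or" plus results by infection reads most naturally as a composite with a breakdown. The abstract's "and" is probably only a condensed list, and the full test specification may sit in an analysis plan that is not shown. That does not answer the main point: the article states both an endpoint and a power, and they do not match.

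**Conclusion.** The point holds as a mismatch without a known direction. The 80% claim in Sample size and the 50% decline claim in the limitations text are not supported for the primary outcome as defined, and the power for that outcome cannot be computed from the documents.

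At 8 v 8, k = 0.42 and 65 tested, the two-infection baseline is 60%. The composite has 63–68% if trichomonas also halves, about 60% if it falls by about 40%, and 27–54% if it falls by 0–25%. At 100 tested the baseline is 66%, with 68–72% and 29% to about 60% in the same two outer cases.

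These figures rest on the assumed 3 to 10 points of trichomonas-only positives and on the composite having the same coefficient of variation as the two infections. Levels also depend on k: the stated standard deviation of 8.45% over 15% gives 0.563 rather than 0.42, and the two-infection baseline at 65 tested is then 44%.

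**What to change.** Keep the three-infection primary outcome. It matches the second objective, on curable STIs, and the trial's stated focus on three infections, so nothing here argues for moving trichomonas to a secondary outcome.

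- In Outcome measures, state that the first primary outcome is one composite test (positive for any of the three), with results by infection as supporting. Align the abstract's wording.
- In Sample size, give the assumed control prevalence, between-cluster variation and effect for that composite, with the resulting power at the planned 100 per cluster and 8 v 8 clusters. If no trichomonas data are available, show a range of assumed responses.
- Until that is done, limit the power statements in Sample size and in the limitations text to chlamydia and gonorrhoea.

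This is a text change. Trial conduct and data collection stay as planned, because all three infections are tested for anyway. The cost is a stated power that may be less favourable or less certain than 80%.

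### The sample size section gives 65 people tested per cluster, the survey it sizes targets 100, the article does not link the two, and the stated 14 clusters follows from neither

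*Protocol article*

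**What the plan says.** The Sample size section names its method: "Power calculations were performed using the method of Hayes and Bennet [34] for cluster randomised trials". Variability is taken from 2006 prevalence data "among Aboriginal people aged 14–34 years in central Australia". The main inputs follow: a prevalence of 15%, "with an average 65 people tested in each cluster for chlamydia and gonorrhoea". The section adds that "between community variability was estimated as corresponding to a standard deviation of 8.45" per cent, and gives "the within community co-efficient of variation of 0.42". From these it concludes that 14 clusters in total, split equally, detect a fall from 15% to 7.5% with 80% power at two-sided 0.05. It says that differing average numbers screened were allowed for, but gives no numbers for that allowance.

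The first primary outcome is prevalence at ages 16–34 as measured by the trial's own survey. Table 2 describes that survey: "50 men and 50 women from each cluster will be included". The Prevalence assessment section agrees: "The assessment will involve screening 50 male and 50 female resident clients aged 16–34 years per cluster". It then refers to the 50 and 50 as targets, shared among the health services of a cluster.

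The Study design and Randomisation sections give 24 clusters entering in three rounds of eight. The Statistical analysis plan section names two main analyses: first round against second at one year, and first against third at two years. Each sets 8 clusters against 8.

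**The concern.** One endpoint has two cluster sizes, 65 and 100, and no sentence connects them. A reader cannot tell whether the precision claim describes the survey as planned or a survey that falls a third short of its target (35 of 100).

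The number tested per cluster enters the binomial part of the variance. It therefore moves the required number of clusters, the power and the smallest detectable reduction. The article also says, in its limitations, that the study is powered for a 50% decline in prevalence. That claim should be traceable to the survey being run, and anyone who recalculates it must first decide which cluster size to use. The inputs also come from a slightly wider age band (14–34) than the endpoint (16–34), without comment.

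**Working it through.** **Inputs from the Sample size section.** p0 = 0.15, p1 = 0.075, two-sided alpha 0.05, power 80%, equal arms, m = 65. The alternative m = 100 comes from Table 2 and the Prevalence assessment section. The coefficient of variation k = 0.42 is used as the between-cluster value that the formula requires, although the article labels it as within community. This is an assumption, and larger values are shown below.

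**Formula (Hayes–Bennett, unmatched proportions).**

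V = [p0(1 − p0) + p1(1 − p1)]/m + k²(p0² + p1²)

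c per arm = 1 + (1.96 + 0.842)² × V/(p0 − p1)²

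Here (1.96 + 0.842)² = 7.849 and (p0 − p1)² = 0.005625. The binomial numerator is 0.1275 + 0.069375 = 0.196875. The between-cluster term is 0.1764 × 0.028125 = 0.004961.

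**Attempt to reproduce the stated 14.**

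- m = 65: V = 0.003029 + 0.004961 = 0.007990, so c = 1 + 11.15 = 12.15. This is 13 per arm, 26 in total (24 without the added 1).
- m = 100: V = 0.001969 + 0.004961 = 0.006930, so c = 1 + 9.67 = 10.67. This is 11 per arm, 22 in total (20 without the added 1).
- One-sided and without the added 1, the totals are 18 at m = 65 and 16 at m = 100, but the article states a two-sided test.
- Among the variants tried, 14 appeared only when both the binomial term and the added 1 were dropped: 7.849 × 0.004961/0.005625 = 6.92, so 7 per arm. Cluster size then plays no part.

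The stated 14 is therefore not reproduced at either size.

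**Power of the planned 8 v 8 comparisons.** Power = Φ(√[7 × 0.005625/V] − 1.96).

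- m = 65: Φ(2.220 − 1.96) = 0.60.
- m = 100: Φ(2.384 − 1.96) = 0.66.
- With the 7 per arm that a total of 14 implies: 0.54 and 0.60.

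**Smallest reduction detectable with 80% power, 8 v 8.** Solve 7(p0 − p1)² = 7.849 × V for p1, with V depending on p1.

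- m = 65: p1 = 0.0589, a 61% reduction.
- m = 100: p1 = 0.0642, a 57% reduction.

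**Sensitivity to k.** The stated standard deviation gives 0.0845/0.15 = 0.563. Net of binomial error at m = 65 it gives √(0.0845² − 0.1275/65)/0.15 = 0.48.

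| k | clusters per arm, m = 65 | clusters per arm, m = 100 | 8 v 8 power, m = 65 | 8 v 8 power, m = 100 |
|---|---|---|---|---|
| 0.42 | 13 | 11 | 60% | 66% |
| 0.48 | 15 | 13 | 53% | 58% |
| 0.563 | 18 | 17 | 44% | 48% |

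**The case against.** A target of 100 and a planning average of 65 can coexist. The Prevalence assessment section treats 50 and 50 as targets. A cluster may be a single community, and a community needs only 100 Aboriginal residents aged 16–34 to be eligible. Only clinic attenders are offered testing, people tested in the previous three months are excluded, and the article admits that the share who do not attend is unknown. Planning below target is ordinary, and the sample size text does claim an allowance for varying numbers screened. This stands: the two figures are unreconciled, but they need not conflict.

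A reader might infer that 65 belongs to a different survey and was carried over by mistake. The text does not support that. It reports 65 next to the 2006 data but does not say whether it describes those data or the trial's expected yield.

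A reader might also infer that the mismatch inflates the claimed power. It does the reverse. At k = 0.42, using 65 asks for 26 clusters rather than 22 and gives 6 points less power.

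Borrowing prevalence and variability from the most recent available data is routine, and ages 16–34 lie within 14–34. The article allows no estimate of what the age difference does, and nothing shows that data restricted to 16–34 exist. The age point is therefore a caveat only.

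The objection does not rescue the stated total. Whichever reading of 65 is right, 14 clusters do not give 80% power under the stated method and inputs.

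**Conclusion.** The point holds in a limited form. The article leaves unexplained how 65 tested per cluster relates to the survey target of 100, and its 14 clusters for 80% power follows from neither.

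The effect of cluster size alone is modest: 26 against 22 clusters in total, and about 60% against 66% power for 8 v 8, at k = 0.42. The remaining gap to 80% is not caused by the choice between 65 and 100. It remains at both sizes and widens with a larger coefficient of variation. On these figures, each planned comparison detects a reduction of about 57% (at 100) to 61% (at 65) with 80% power, not the 50% claimed.

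This rests on four assumptions: 0.42 is the between-cluster coefficient of variation and is the same in both arms, cluster sizes are equal, each main analysis is a plain comparison of 8 with 8 clusters, and precision gains nothing from the baseline survey.

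**What to change.** In the Sample size section:

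- State what 65 represents: the average in the 2006 data, or the expected yield of the trial survey.
- Restate the required number of clusters, the power of the 8 v 8 comparisons and the detectable reduction at the planned 100 per cluster. With k = 0.42 these are 11 per arm (22 in total), about 66%, and about 57%.
- Show 65 as a labelled shortfall case: 13 per arm (26 in total), about 60%, and about 61%.
- Note that the source data cover ages 14–34 and the endpoint 16–34, as a limitation of the inputs.

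Leave the survey target of 100 per cluster unchanged in Table 2 and the Prevalence assessment section. Lowering it to 65 would remove the discrepancy only by giving up precision.

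The work is one recalculation and a few sentences, with no change to recruitment or procedures. The downside is that the stated power becomes less favourable, and the claim of power for a 50% decline must be brought into line.

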Secondly the STRIVE study is powered to detect a 50% decline in STI prevalence but it is possible that reductions may be less than this. However, a 50% reduction in prevalence would still leave rates at between 4 and 30 times higher, and the level of STI care provided after the SHQIP program will still be comparable to what is provided in health services accessible to Australians not living in remote communities.

Other key challenges to STRIVE are those characteristic of remote environments and include the need to sustain the motivation of clinic staff to participate in STRIVE while addressing the multiple competing health priorities, as well as high staff turnover.

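### The sample-size paragraph's 14 clusters in total for 80% power does not follow from its own method and inputs, and the planned 8 v 8 comparisons have about 60 to 66% power at the stated coefficient of variation

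*Protocol article*

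**What the plan says.** All of this is in the protocol article.

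- **Method (Sample size).** "Power calculations were performed using the method of Hayes and Bennet [34] for cluster randomised trials".
- **Baseline and cluster size (Sample size).** "Prevalence of chlamydia and gonorrhoea was estimated to be 15%, with an average 65 people tested in each cluster for chlamydia and gonorrhoea".
- **Variability (Sample size).** "between community variability was estimated as corresponding to a standard deviation of 8.45%, and the within community co-efficient of variation of 0.42".
- **Result (Sample size).** "A total of 14 clusters are needed to detect a reduction in chlamydia and gonorrhea prevalence from 15% in control clusters to 7.5" per cent "in SHQIP clusters with 80% power and allowing for differing average numbers of people screened in each cluster", at two-sided 0.05 without multiplicity adjustment and with equal arms. Fourteen in total is therefore 7 per arm.
- **Clusters available (Study design; Randomisation).** There are 24 clusters. Eight were allocated in the first round and eight in the second, which leaves eight for the third.
- **Main analyses (Statistical analysis plan).** Round 1 is compared with round 2 after one year, and round 1 with round 3 after two years. Each comparison is 8 v 8.
- **Survey size (Prevalence assessment; Table 2).** 50 men and 50 women per cluster, so 100.
- **Power claim (limitations, at the end of the Statistical analysis plan section).** "Secondly the STRIVE study is powered to detect a 50% decline in STI prevalence".

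**The concern.** The article gives the method, every input and the answer, so the answer can be checked, and it does not reproduce. The variability inputs also disagree with each other. An SD of 8.45% at a prevalence of 15% is not a CV of 0.42, and 0.42 is labelled as within-community although the formula uses a between-cluster CV.

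The stake is how the main comparisons will be read. Set against a stated need of 14 clusters, 16 clusters in an 8 v 8 comparison look more than enough. If the true requirement is much higher, a real halving of prevalence could well be missed, and a null result could be misread as evidence against the quality improvement program.

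**Working it through.** **Inputs.** From Sample size: p0 = 0.15, p1 = 0.075, m = 65 tested per cluster, k = 0.42, two-sided alpha 0.05, power 80%. From Prevalence assessment, as a sensitivity value: m = 100.

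**Formula (Hayes–Bennett, unmatched, clusters per arm).**

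c = 1 + (1.96 + 0.842)² × V / (p0 − p1)², where V = p0(1 − p0)/m + p1(1 − p1)/m + k²(p0² + p1²).

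Inverted for power: Φ(√[(c − 1)(p0 − p1)²/V] − 1.96).

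**Step 1: attempt to reproduce the plan's 14.**

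- V = 0.1275/65 + 0.069375/65 + 0.1764 × 0.028125 = 0.0019615 + 0.0010673 + 0.0049613 = 0.0079901.
- c = 1 + 7.849 × 0.0079901/0.005625 = 12.15, so 13 per arm and 26 in total.

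The stated 14 in total is not reproduced.

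**Step 2: power of 14 in total.** √(6 × 0.005625/0.0079901) = 2.055, and Φ(2.055 − 1.96) = 53.8%. A noncentral t calculation gives 53.2%.

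**Step 3: power of the planned 8 v 8 comparisons.**

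- m = 65: √(7 × 0.005625/0.0079901) = 2.220, so power is 60.3% (noncentral t 59.8%).
- m = 100: V = 0.001275 + 0.00069375 + 0.00496125 = 0.00693; √(7 × 0.005625/0.00693) = 2.384, so power is 66.4%.

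**Step 4: reduction detectable by 8 v 8 at 80% power.** Solving c = 8 for p1 at k = 0.42:

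- m = 65: p1 = 0.0589, a reduction of (0.15 − 0.0589)/0.15 = 61%.
- m = 100: p1 = 0.0642, a reduction of 57%.

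**Step 5: the two variability figures.** 8.45/15 = 0.563, not 0.42. A CV of 0.42 with SD 8.45% would need a mean of 8.45/0.42 = 20%. With k = 0.563:

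- m = 65: V = 0.0019615 + 0.0010673 + 0.0089253 = 0.0119542; c = 17.68, so 18 per arm. Power is 39% for 7 v 7 and 44% for 8 v 8.
- m = 100: c = 16.20, so 17 per arm. Power for 8 v 8 is 48%.

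**Step 6: can another reading give 7 per arm?** Each line changes one element and keeps k = 0.42 as the between-cluster CV.

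| Change | Clusters per arm |
|---|---|
| m = 100 | 10.67, so 11 |
| Unlimited testing per cluster | 7.92, so 8 |
| Without the added 1 | 11.15, so 12 |
| One-sided alpha | 9.78, so 10 |
| Matched version (adds 2) | 13.15, so 14 pairs, 28 clusters |

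Dropping both the sampling term and the added 1 gives 6.92, but that ignores the stated 65 per cluster. Seven per arm at m = 65 would need k of about 0.21, half the stated value. Unequal cluster sizes raise the requirement: an effective m of 50, assumed for illustration, gives 13.42.

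**The case against.** **The survey is larger than 65.** The plan fixes 100 per cluster, so 66% is as fair a figure for 8 v 8 as 60%. This stands, and both are given. Neither reaches 80%.

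**The label on 0.42 is unclear, so it may not be the between-cluster CV.** If 0.42 is total observed variation and binomial error at 65 tested is removed, k = √(0.063² − 0.1275/65)/0.15 = 0.30. At m = 100, 8 v 8 would then have 84% power and 7 v 7 78%. This is the most favourable reading, and it shows why the CV must be clarified. It does not rescue the printed sentence: at the stated 65, k = 0.30 needs 8.73, so 9, per arm. The printed SD also points the other way, towards a larger CV.

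**The primary outcome also includes trichomonas.** A composite would have a higher baseline. With assumed baselines of 20 to 30%, m = 100 and k = 0.42, 8 v 8 power for a halving is 70 to 74%. That softens the shortfall without removing it.

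**Consequences.** The plan requires 95% confidence intervals and itself warns that the reduction may be below 50%. So a null result could be misread, but it is not certain to be.

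**Stronger readings that the documents do not support.**

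- A reader might infer that 14 was a per-arm figure printed as a total. Several routes lead to 14, and nothing in the article selects one. Fourteen per arm would also be 28 clusters, more than the 24 recruited.
- A reader might infer that the trial as a whole cannot reach 80%. Baseline adjustment or an analysis using all steps could raise power. However, the sample-size paragraph claims neither, and the main analyses are defined as two-group comparisons.
- A reader might infer the reverse, that using all 24 clusters restores 80%. A plain 12 v 12 split gives 79.5% (m = 65) or 85% (m = 100) at k = 0.42, but only 62% or 66% at k = 0.563. Neither describes a stepped-wedge model.

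**Conclusion.** The point holds. On the article's named method and printed inputs, 80% power needs 13 clusters per arm (26 in total), and 14 in total gives about 54%. At a between-cluster CV of 0.42, the 8 v 8 main comparisons have about 60% power with 65 tested per cluster and 66% with 100. They would miss a true halving in roughly 34 to 40% of trials. At the CV of 0.56 implied by the stated SD, power is about 44 to 48%.

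The statement that the study is powered for a 50% decline is therefore not supported for the analyses that the plan defines as main. The SD and CV cannot be reconciled as printed, and the article does not show which is wrong.

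These figures assume the unmatched formula, an unadjusted two-group comparison, equal cluster sizes, and 0.42 or 0.56 as the between-cluster CV. This is an error in a stated result, which details held in a fuller analysis plan would not make right.

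**What to change.** 1. Correct the sample-size paragraph. At the stated inputs (65 tested, between-cluster CV 0.42) the requirement is 13 clusters per arm, 26 in total.
2. State one between-cluster CV, label it as such, and reconcile it with the SD of 8.45%, including the mean to which that SD refers.
3. Replace the claim that 14 in total gives 80% power, and the limitations statement about a 50% decline, with the power or detectable effect of the 8 v 8 comparisons. At CV 0.42 this could read:

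> Each main comparison of 8 with 8 clusters has about 60% power (65 tested per cluster) to 66% power (100 tested) to detect a fall from 15% to 7.5%. At 80% power, the detectable reduction is about 61% and 57% respectively.

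4. If an analysis using all 24 clusters is adopted as main, give the power computed for that model instead.

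**Cost.** Text only; no new clusters and no change to the surveys. The downside is that the stated power becomes less favourable.
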